### Safety reporting

5.6

This study will be conducted in accordance with the protocol, ISO 14155 (Good Clinical Practice), and applicable national and European regulations, including GDPR (EU 2016/679), the EU Medical Device Regulation (MDR 2017/745) and relevant Belgian legislation.

Adverse events (AEs) will be reported from the first use of the medical device until the last study‐related activity. Events occurring between informed consent and first device use will be recorded as medical history. All (S)AEs will be documented in the patient file and eCRF, except hospitalizations for social reasons or unchanged pre‐existing conditions. All serious adverse events (SAEs) and device deficiencies will be reported to the sponsor/national coordinator and monitor within three calendar days using the appropriate forms, with follow‐up information provided as required.

### Authorization

5.7

This study obtained approval from the Regulatory Authorities (RA) prior to the start of the study. Substantial protocol modifications will be submitted to the RA during the course of the study according to the requirements and within the timelines as defined by the national law. Substantial modifications will only be implemented after approval of the RA. The submission package will include a cover letter including a rationale or justification of the changes (point by point), a list of documents submitted, an application form, amended documents in track change and clean version and any other documents that may be relevant for the assessment of the modification as applicable.

### Monitoring

5.8

Regular monitoring will be performed by HIRUZ CTU according to ICH GCP and ISO 14155. Data will be evaluated for compliance with the protocol and accuracy in relation to source documents. Following written standard operating procedures, the monitors will verify that the clinical investigation is conducted and data are generated, documented and reported in compliance with the protocol, ISO 14155 and the applicable regulatory requirements. An initiation visit, routine monitoring visits and a final visit after the last patient had finished the study. The frequency, extent and nature of the monitoring will depend on the risk assessment of the study.

### Analysis plan

5.9

Statistical analysis will be performed by the investigating team, with the support of the Biostatistics Unit of Ghent University.

#### Summary of baseline data

5.9.1

Descriptive statistical analyses will be performed for patient characteristics. Tests of statistical significance will not be undertaken for baseline characteristics; rather, the clinical importance of any imbalance will be noted.

#### Primary estimand

5.9.2

Our primary estimand is the absolute difference in proportion of favourable outcome (planning and performing as planned a SC strategy) between the DIPLANN‐tool in combination with conventional CT imaging and conventional CT imaging alone, in patients diagnosed with localized kidney cancer who are planned to undergo renal cancer surgery and *in whom SC is deemed possible* either according to the DIPLANN‐tool in combination with conventional CT imaging or according to conventional CT imaging only. Intercurrent events such as cancellation or postponement of the surgical procedure of a randomized patient outside of the study time limit will be dealt with using a composite strategy: the surgical procedure of a patient with such an intercurrent event is considered to have an unfavourable outcome. Given that we expect these intercurrent events to occur equally in both arms, this will lead to a conservative estimate of the risk difference. Intercurrent events such as major protocol deviations and a switch in the medical device used for planning the surgical procedure will be dealt with using the treatment policy strategy to determine the effect including all outcomes regardless of these intercurrent events occurring (similar to the intention to treat principle).

#### Primary estimator (primary analysis) and estimate

5.9.3

We will apply a statistically reliable method of covariate adjustment to estimate the marginal risk difference as an unconditional treatment effect. This standardized estimator is recommended in the U.S. Food and Drug Administration Guidance on covariate adjustment (FDA 2023).

A binary logistic regression model will be fitted with maximum likelihood on each arm separately to regress the primary endpoint on hospital and the highest individual PADUA classification (low (<8), intermediate (8–9) and high‐risk (>9)). The model will include an intercept term. The probability of a favourable primary outcome will be predicted for all subjects twice: once based on the model fitted on the arm assigned to the DIPLANN‐tool in combination with conventional CT imaging, and once based on the model fitted on the arm with conventional CT imaging alone. Hence, there are two scenarios under which the counterfactual probabilities are calculated: 1) everyone is assigned to DIPLANN‐tool in combination with conventional CT imaging, 2) everyone is assigned to conventional CT imaging alone.

The average responses under both scenarios are estimated by averaging the respective counterfactual probabilities across all subjects. These estimates of average response rates in the two treatment groups are used to estimate the unconditional absolute risk difference.

A confidence interval (CI) around the marginal risk difference will be computed using the non‐parametric BCa bootstrap method (Efrond and Tibshirani 1994).

This analysis will include all randomized patients in whom SC was deemed possible, either according to the DIPLANN‐tool in combination with conventional CT imaging or according to conventional CT imaging only.

#### Interim analysis for efficacy

5.9.4

When 50% of the primary endpoints are measured, a non‐binding interim analysis for efficacy for the primary objective and primary estimand will be performed at the 0.88% significance level (z = 2.37, based on O'Brien Fleming group sequential boundaries).

The final analysis of the primary endpoint will be performed at the 4.67% significance level (z = 1.68).

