### Sample size determination

5.3

The study is powered for its primary objective, which targets patients in whom SC is deemed possible either according to the DIPLANN‐tool in combination with conventional CT imaging or according to conventional CT imaging only, as assessed by an independent surgeon between inclusion and randomization.

A sample size of 196 patients in whom SC is deemed possible is needed to achieve at least 80% power to detect an absolute risk difference of 15.6% in favourable outcome (planning and performing as planned a SC strategy) between the DIPLANN‐tool in combination with conventional CT imaging and conventional CT imaging alone, using an exact binomial test at the two‐sided 5% significance level when the design is balanced (1:1 allocation ratio) and the true rate of favourable outcome is 73.4% with conventional CT imaging alone and 89.0% with the DIPLANN‐tool in combination with conventional CT imaging.

The sample size was increased to 198 patients to allow for a 1% drop‐out. The sample size was further increased to 202 patients in whom SC is deemed possible (101 in each group), to foresee an interim analysis for efficacy when 50% of the primary endpoints are measured, using a group sequential design with O'Brien Fleming alpha spending function.

When SC is deemed possible in 86% of patients, the total sample size of patients diagnosed with localized kidney cancer who are planned to undergo renal cancer surgery will be 235. The assumed rate of SC performed as predicted, with a standard of care of 73.4%, is based on other studies.^6^, ^7^

Recruitment will continue until 202 patients in whom SC is deemed possible are randomized.

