#### Significance level and confidence intervals

5.9.11

The nominal type I error rate will be controlled at 5%. The hierarchy of endpoint families will be respected. Analysis of secondary endpoints will only be interpreted after demonstration of success on the primary estimand.

The interim analysis for the primary estimand will be performed at the 0.88% significance level and the final analysis at the 4.67% significance level (based on O'Brien Fleming group sequential boundaries).

Bonferroni correction for multiple testing due to multiple key secondary estimands will be applied, setting the significance level at 1.67%.

Subgroup analyses and analyses of other endpoints will be considered as exploratory and hypothesis‐generating.

Any deviation(s) from the original statistical analysis plan will be recorded as a note to file and reported in the final clinical investigation report and publication.

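### The interim and final boundaries (0.88%, z = 2.37; 4.67%, z = 1.68) belong to a one-sided 5% O'Brien-Fleming design, although the trial is planned at two-sided 5%

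*Protocol article*

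**What the plan says.** - **Section 5.3, sample size.** The primary comparison is powered "using an exact binomial test at the two‐sided 5% significance level when the design is balanced (1:1 allocation ratio"). The interim look is added "using a group sequential design with O'Brien Fleming alpha spending function".
- **Section 5.9.4, interim analysis.** With half of the primary endpoints measured, the efficacy analysis "will be performed at the 0.88% significance level (z = 2.37"). For the end of the trial: "The final analysis of the primary endpoint will be performed at the 4.67% significance level (z = 1.68"). The basis given is O'Brien-Fleming group sequential boundaries, without mention of a spending function.
- **Section 5.9.11, significance level.** "The nominal type I error rate will be controlled at 5"%. The levels 0.88% and 4.67% are repeated there, without z values.

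Neither 5.9.4 nor 5.9.11 says whether its levels are one-sided or two-sided. The only statement on sidedness is the one in 5.3.

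**The concern.** A z of 2.37 and a level of 0.88% agree only as a one-sided tail area, and the same is true of 1.68 and 4.67%. In a two-sided 5% design the final critical value cannot fall below 1.96, because spending some error at an interim look can only push it higher. A printed 1.68 is therefore a warning by itself.

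These numbers are the success criteria of a trial that section 2 describes as confirmatory and pivotal. They decide whether the tool is declared effective early and whether it is declared effective at the end. Section 5.9.11 also makes interpretation of the secondary endpoints depend on success with the primary estimand, so excess error there carries down the hierarchy. The two printed forms can also give opposite verdicts on the same data: a final z between 1.68 and 1.99, or an interim z between 2.37 and 2.62, is a success by the z value and a failure by the percentage read as two-sided.

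**Working it through.** **Inputs.** Two-sided 5%, rates of 73.4% and 89.0%, at least 80% power, 196 patients rising to 198 and then 202 (section 5.3); one interim look at 50% of the primary endpoints, for efficacy only, with the four printed boundary figures (section 5.9.4).

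**1. Which sidedness does the sample size use?** Normal approximation with pooled variance under the null hypothesis, per arm:

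n = [z_α √(2p̄q̄) + z_β √(p₁q₁ + p₂q₂)]² / δ²

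with p̄ = 0.812, √(2p̄q̄) = 0.5526, √(p₁q₁ + p₂q₂) = 0.5414, δ = 0.156.

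- Two-sided 5%: (1.960 × 0.5526 + 0.8416 × 0.5414)² / 0.02434 = 97.3, so 98 per arm and 196 in total. This is the plan's figure.
- One-sided 5%: the same formula with 1.645 gives 76.5, so 77 per arm and 154 in total (178 with continuity correction).

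The 196 is thus a two-sided figure.

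**2. Tail areas of the printed z values.**

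| z | one-sided | two-sided | printed level |
|---|---|---|---|
| 2.37 | 0.89% | 1.78% | 0.88% |
| 1.68 | 4.65% | 9.30% | 4.67% |

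The other way round, 0.88% and 4.67% as two-sided levels correspond to z = 2.62 and 1.99.

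**3. Boundaries for two looks at 50% and 100% information.** Z₁ and Z₂ are bivariate normal with correlation √0.5. The classical O'Brien-Fleming shape sets c₁ = √2 · c₂ and solves for the overall error. The spending function version spends 2 − 2Φ(z_{α/2}/√0.5) at the interim. With α = 2.5% per side that is 0.1525% per side, or 0.31% two-sided.

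| Design | z interim / final | levels |
|---|---|---|
| Classical, one-sided 5% | 2.373 / 1.678 | 0.882% / 4.668% (one-sided) |
| Classical, two-sided 5% | 2.797 / 1.977 | 0.52% / 4.80% (two-sided) |
| Spending function, one-sided 5% | 2.538 / 1.662 | 0.56% / 4.82% (one-sided) |
| Spending function, two-sided 5% | 2.963 / 1.969 | 0.31% / 4.90% (two-sided) |

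Only the first row reproduces the plan, and it reproduces all four figures to rounding.

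**4. Overall error of the printed rules.** For critical values c₁ and c₂, with φ and Φ the standard normal density and distribution function:

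error = 1 − ∫ from −c₁ to c₁ of φ(x) · [Φ((c₂ − √0.5·x)/√0.5) − Φ((−c₂ − √0.5·x)/√0.5)] dx

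- z values used (2.37 / 1.68): 9.97% two-sided, of which 4.98% is in favour of the tool.
- Percentages used as two-sided levels (2.62 / 1.99): 5.07% two-sided, 2.54% in favour of the tool. With 0.88% spent at the interim, the final level would have to be 4.60%, not 4.67%, to hold 5%.

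**5. A supporting sign in the sample size.** The inflation factor for one interim look is 1.0155 in the classical one-sided 5% design: 198 × 1.0155 = 201.1, or 202 as the next even number, which is the plan's figure. In the classical two-sided design the factor is 1.0075: 198 × 1.0075 = 199.5, or 200. The step from 198 to 202 therefore fits the same one-sided calculation.

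**The case against.** The strongest reply is that the percentages govern. Section 5.9.4 defines each analysis by its significance level and gives z only in parentheses; section 5.9.11, which deals with error control, prints no z at all; and the primary inference in section 5.9.3 is a BCa bootstrap interval, which needs a confidence level and produces no z statistic. Read as two-sided levels, 0.88% and 4.67% exceed 5% by only 0.07 percentage points. This is a fair point and it limits the headline: the doubling is the consequence of one of two readings. It does not remove the problem, because the article prints both forms as the rule, they disagree once the test is two-sided, and the gentler reading still exceeds 5%.

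A second reply is that section 5.9.4 is coherent as a one-sided 5% boundary and that 5.9.11 does not say two-sided. That is true of those two sections taken alone. Section 5.3 does say two-sided, however, and 196 follows only from that. A one-sided 5% rule would relax the planned error without saying so.

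Third, the mismatch with the spending function is secondary. Sections 5.9.4 and 5.9.11 speak of boundaries, which suits the classical form. Measured against 0.31%, the interim threshold is 2.9 times too large (0.88%) or 5.8 times (1.78%); against the classical 0.52% the ratios are about 1.7 and 3.4. Which variant is meant is the sponsor's choice. The level of the bootstrap interval and the recalculation at the actual information fraction could also be left to the analysis plan, so their absence is not an error.

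**Conclusion.** The concern holds. The printed boundaries are those of a one-sided 5% design placed in a trial that is planned and sized at two-sided 5%. The z values double the error, to 9.97% two-sided; the percentages read as two-sided give 5.07%. Neither delivers the error rate the plan claims, and the document does not say which form decides. This must be corrected before the interim analysis, since changing a boundary once unblinded data have been seen would be hard to defend.

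The calculation assumes an interim at exactly 50% information, a test statistic that is approximately normal with independent increments, stopping for efficacy only, and the spending function applied at 2.5% per side. The match with the one-sided design is exact to rounding; that it arose by entering one-sided 5% in place of 2.5% per side is an inference from that match.

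**What to change.** In sections 5.9.4 and 5.9.11, state that both tests are two-sided, name one boundary family, and print z and percentage values that agree:

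- **Spending function, as named in section 5.3:** interim 0.31% (|z| ≥ 2.96), final 4.90% (|z| ≥ 1.97).
- **Classical O'Brien-Fleming, if that is meant:** interim 0.52% (|z| ≥ 2.80), final 4.80% (|z| ≥ 1.98), with section 5.3 reworded to match.

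The figures apply at exactly 50% information; under the spending function, recompute the final level from the actual fraction. It is also worth stating the matching level of the BCa interval used for the decision: 99.69% and 95.10% for the spending function (100 − 0.31 and 100 − 4.90), or 99.48% and 95.20% for the classical form.

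The cost is wording in the protocol and the analysis plan. No more patients are needed: the classical two-sided design requires 196 × 1.0075 = 197.5 evaluable patients and the spending function 196 × 1.0040 = 196.8, while 202 less 1% drop-out leaves 202 × 0.99 ≈ 200. The price is a somewhat lower chance of stopping early.

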#### Subgroup analyses

5.9.5

To explore the heterogeneity of the primary estimand, subgroup analyses will be performed for the following subgroups:Hospital where surgery is performed (Ghent University Hospital vs AZ Maria Middelares Hospital vs other hospitals).Kidney function (eGFR < 30, [30–45[, [45–60[, ≥ 60).Highest individual PADUA classification (low (<8), intermediate (8–9) and high‐risk (>9)).

#### Key secondary estimand 1 and estimator

5.9.6

One of our key secondary estimands is very similar to the primary estimand, but targets a different patient population, namely all patients diagnosed with localized kidney cancer who are planned to undergo renal cancer surgery (regardless of whether SC is deemed possible). The analysis will be similar to the analysis for the primary estimand, but will include all randomized patients and will be adjusted for whether SC was deemed possible by the independent surgeon (as a main effect).

#### Key secondary estimand 2 and estimator

5.9.7

Another key secondary estimand is the difference in mean change from baseline (preoperative) in eGFR at 6 months postoperatively, between the DIPLANN‐tool in combination with conventional CT imaging and conventional CT imaging alone, in all patients diagnosed with localized kidney cancer who are planned to undergo renal cancer surgery.

Because eGFR is measured repeatedly (preoperatively, POD1, last measurement before discharge, postoperatively 1 month, 3 months, 6 months, 12 months), we will fit a linear mixed model for eGFR with a random intercept for patient, including time, arm, a two‐way interaction between time and arm and the stratification factors: whether SC is deemed possible, hospital and highest individual PADUA classification in the fixed effects part of the model.

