## STUDY DESIGN

2

PODRACING (Planning Operative strategy using a Digital Renal Artery ClampING tool) is a confirmatory, multicentric, unblinded, randomized, controlled, pivotal trial using parallel group assignment and stratified randomization.

Patients will be randomized according to a 1:1 allocation ratio to either the experimental group (the DIPLANN‐tool in combination with conventional CT imaging) or the control group (conventional CT imaging alone), using permuted block randomization with blocks of varying size.

Randomization will be stratified by the following variables:Whether SC is deemed possible either according to the DIPLANN‐tool in combination with conventional CT imaging and/or according to conventional CT imaging only, as assessed by an independent surgeon (between inclusion and randomization) who will not be involved in the RAPN surgical procedure (yes vs no), see 5.2 ‘study procedures’ for more details.Hospital where surgery is performed (Ghent University Hospital vs AZ Maria Middelares Ghent vs AZORG Hospital Aalst vs AZ Sint‐Jan Bruges vs ZOL Genk).PADUA classification (low (<8) and intermediate (8–9) vs high‐risk (>9)). In case of multiple masses, the mass with the highest individual PADUA classification will be used.A static randomization list was developed by an independent statistician and uploaded in the randomization module of REDCap to allow for automated randomization.

The study will be rolled out in five high‐volume hospitals in Belgium (Ghent University Hospital, AZ Maria Middelares Ghent, AZORG Hospital Aalst, AZ Sint‐Jan Bruges and ZOL Genk), including surgeons with different ranges of experience in RAPN and in 3D modelling. We aim to randomize 235 patients diagnosed with localized kidney cancer who are planned to undergo renal cancer surgery.

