#### Other analyses

5.9.9

Endpoints that are measured repeatedly will be analysed using generalized linear mixed models with a random intercept for patient, including time, arm, a two‐way interaction between time and arm and the stratification factors: whether SC is deemed possible, hospital, and the highest individual PADUA classification in the fixed effects part of the model.

Continuous endpoints measured at one point in time will be analysed using a linear regression model including arm and the stratification factors: whether SC is deemed possible, hospital and the highest individual PADUA classification. Log‐normally distributed endpoints will be log‐transformed before analysis.

Binary endpoints measured at one point in time will be analysed using a binary logistic regression model (with logit link function), including arm and the stratification factors: whether SC is deemed possible, hospital and the highest individual PADUA classification.

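### The key secondary eGFR model has only a random intercept across seven visits, so its standard error for the 6-month change is right only under one variance and one correlation throughout; it also makes no use of baseline eGFR to gain precision

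*Protocol article*

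**What the plan says.** Section 5.9.7 of the protocol article defines the estimand as "the difference in mean change from baseline (preoperative) in eGFR at 6 months postoperatively", compared between arms in all patients. It notes that "eGFR is measured repeatedly (preoperatively, POD1, last measurement before discharge, postoperatively 1 month, 3 months, 6 months, 12 months", and then fixes the model: "we will fit a linear mixed model for eGFR with a random intercept for patient". The fixed effects are arm, visit, their interaction and the three factors used to stratify randomisation. The pre-operative value is therefore one of the seven outcomes. The section names no residual covariance structure, random slope, robust standard error, baseline covariate or common baseline mean.

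Section 5.9.9 gives other repeated endpoints the same form: "Endpoints that are measured repeatedly will be analysed using generalized linear mixed models with a random intercept for patient".

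Section 5.9.11 tests the key secondary estimands with a Bonferroni correction, "setting the significance level at 1.67"%. Section 5.9.10 relies on likelihood-based longitudinal analysis being valid when outcomes are missing at random. Table 3 (section 5.2) places the pre-operative blood test at the pre-op visit, which is after allocation and before surgery.

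**The concern.** A random intercept with independent residuals is compound symmetry. It makes the pre-operative and 6-month values as strongly correlated as the 3-month and 6-month values, and the day-1 value as variable as the 12-month value. Surgery falls between the first measurement and the other six, and two of those six come from the hospital stay, so there is reason to doubt this. Two departures are easy to imagine, and they act in opposite directions:

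- If the loss of function differs between patients and persists, post-operative values correlate more with each other than with the pre-operative value. The pooled residual variance is then too small for the 6-month change.
- If the day-1 and discharge values are noisier than the rest, the pooled residual variance is too large.

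This estimand carries part of the 5% error control, and that control needs a correct standard error. Missing data add a second dependence: a missing 6-month value is in effect predicted from the patient's other values with equal weight on each visit, which is appropriate only if the covariance is right.

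The mean model raises a separate and smaller issue. With arm, time and their interaction all free, the pre-operative mean is estimated separately in each arm. The 6-month contrast is then a plain change score, and baseline eGFR is not used to reduce variance.

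**Working it through.** **Inputs from the article.** Seven visits, so 21 visit pairs: 6 pre/post and 15 post/post. Allocation: "Patients will be randomized according to a 1:1 allocation ratio". Total: "the total sample size of patients diagnosed with localized kidney cancer who are planned to undergo renal cancer surgery will be 235"; 202/0.86 = 234.9 reproduces it. Level 0.05/3 = 1.67%, two-sided critical value 2.394. The article gives no eGFR standard deviation, correlation, effect size or power, so there is no eGFR figure to reproduce.

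**Assumptions.** Complete data, SD 20 at each visit unless stated, and the correlations listed below. The SD cancels from the ratio when it is the same at every visit.

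**Formulas.** With complete data and a saturated time-by-arm model, the random-intercept estimate equals the difference in raw mean change (confirmed by fitting the model to simulated data). Per patient:

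- variance of change implied by the model: M = 2 × (mean visit variance − mean pairwise covariance)
- true variance of change: T = V(pre) + V(6m) − 2 × C(pre, 6m)
- model SE / true SE: r = √(M/T)
- actual level of the test: 2 × (1 − Φ(2.394 × r))

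**Two cases in full.**

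- *Correlation 0.85 pre/post, 0.92 post/post.* Mean correlation (6 × 0.85 + 15 × 0.92)/21 = 0.90. M = 800 × 0.10 = 80; T = 800 × 0.15 = 120; r = 0.82; level 5.1%.
- *The same, but day 1 and discharge have SD 23 and correlation 0.75 with every other visit and with each other.* Mean variance (5 × 400 + 2 × 529)/7 = 436.9. Mean covariance (1 × 396.75 + 10 × 345 + 4 × 340 + 6 × 368)/21 = 353.1. M = 167.5; T = 120; r = 1.18; level 0.5%.

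**All cases.**

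| Assumed covariance | Model SE / true SE | Actual level at nominal 1.67% |
|---|---|---|
| Compound symmetry, 0.80 | 1.00 | 1.67% |
| 0.85 pre/post, 0.92 post/post | 0.82 | 5.1% |
| 0.80 pre/post, 0.92 post/post | 0.76 | 7.0% |
| Correlation decaying 0.90 per visit step | 0.76 | 6.9% |
| Correlation decaying 0.95 per visit step | 0.74 | 7.5% |
| 0.85 for all other pairs; early visits SD 23, correlation 0.75 | 1.24 | 0.3% |
| 0.80/0.92; early visits SD 23, correlation 0.75 | 1.05 | 1.2% |
| 0.85/0.92; early visits SD 23, correlation 0.75 | 1.18 | 0.5% |
| 0.85/0.92; early visits SD 23, correlation 0.85 | 0.995 | 1.7% |
| Extra noise at day 1 and discharge only, two strengths | 1.13 to 1.31 | 0.7% to 0.2% |

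Simulation with 235 patients agreed with the formula in the cases tried. For example, the level was 6.85% with 0.90 decay against 6.9% by formula.

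**Baseline mean.** With equal variances, the change score has variance proportional to 2(1 − ρ), and the baseline-adjusted contrast to 1 − ρ². Their ratio is (1 + ρ)/2, so the saving is (1 − ρ)/2: 10% at ρ = 0.80, 7.5% at 0.85 and 5% at 0.90. At 0.85 the standard error falls by about 4% (√0.925 = 0.962).

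**The case against.** **The direction of error is unknown.** A reader might infer that the planned test inflates the type I error, since several scenarios give 5% to 7.5%. The documents do not support that. Those scenarios treat day-1 and discharge values like late ones. Adding early-visit noise to the 0.80/0.92 and 0.85/0.92 cases brings the level down to 1.2% and 0.5%, and with milder noise it is 1.7%. This objection stands: inflation is possible, not shown.

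**The article is condensed.** A structured residual covariance, a robust standard error or a degrees-of-freedom method could sit in an analysis plan that is not shown, and a random intercept excludes none of them. This stands in part. What was left out is no fault, but the random-intercept form is stated positively for this estimand and again in section 5.9.9, and as stated it means compound symmetry.

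**The estimate is sound.** With complete data it is the unbiased difference in mean change, which is what section 5.9.7 targets. This stands. A reader might take the free baseline mean for an error as well; it is a modest loss of efficiency, and no stated eGFR power is affected.

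**Baseline balance is not automatic.** The pre-operative sample follows allocation in an unblinded trial. A common baseline mean therefore needs the assumption that allocation cannot change pre-operative eGFR. That is plausible, but it has to be written down.

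**Missing data may be few.** Section 5.9.10 expects little missingness, so the weakness in the missing-at-random argument may matter little. Its size has not been calculated.

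**Conclusion.** The point holds in conditional form. The stated model gives a correct standard error for the 6-month change if compound symmetry holds, or if the departures from it happen to cancel for this contrast. Otherwise the standard error is wrong. Under the assumed covariances it ranged from 26% too small to 31% too large, with an actual level of about 7.5% down to 0.2%. These figures illustrate sensitivity and do not estimate this trial's error rate.

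The missing-at-random claim rests on the same covariance assumption. The forgone precision is a secondary matter: 5% to 10% of variance for ρ between 0.90 and 0.80.

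The change is worth making because this test is part of the 5% error control and the remedy is free. For the endpoints under section 5.9.9, which section 5.9.11 treats as exploratory, the same weakness matters less.

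**What to change.** In section 5.9.7 or the analysis plan:

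- Use an unstructured covariance over the visits. If that fit does not converge, fall back on the stated random-intercept model with a robust standard error. The fallback repairs the standard error but not the covariance dependence under missing data.
- Either model post-operative eGFR with pre-operative eGFR by visit as a covariate, or keep the pre-operative value as an outcome with one mean common to both arms. For the common mean, state the assumption that allocation cannot affect a blood sample taken after allocation but before surgery.
- Name the arm contrast at 6 months as the test.
- Apply the same covariance approach to the continuous repeated endpoints under section 5.9.9.

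The cost is a few sentences. A 7 × 7 matrix has 7 × 8/2 = 28 parameters, which 235 patients can support. No new data or visits are needed.
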